### Statistical analysis

We used SPSS version 20.0 (IBM Corp, Armonk, NY, USA) for standard statistical analyses. Quantitative variables are presented as the mean ± standard deviation when normality is met. We used one-way analysis of variance (ANOVA) to compare quantitative data. If *p* < 0.5 for ANOVA, LSD or Dunnett’s test was used to compare means. Chi-square analysis or Fisher’s exact test was used to compare qualitative data, and paired sample *t*-tests were used for the same group. Comparisons of unidirectional orderly data were analyzed using the Wilcoxon signed-rank test. Two-sided *P* values were reported when comparing differences between the 2 groups. *P* value < 0.05 was considered of statistical significance.

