**Ethics and dissemination:**

The results of this study will be published in peer-reviewed journals and presented at conferences. Upon completion of this trial, our findings could provide an appropriate cervical collar-wearing guideline for patients receiving HS.

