## Methods

### Study design

This single-center, exploratory, prospective randomized controlled trial will be carried out at the West China Hospital of Sichuan University. Patients who fulfill study entry criteria will be randomly assigned to wear no collar, wear it for 3 weeks, wear it for 6 weeks, and wear it for 12 weeks at a ratio of 1:1:1:1. The study design and protocol were approved by the Ethics Committee on Biomedical Research, West China Hospital of Sichuan University. SPIRIT reporting guidelines were adhered to in this protocol [33].

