### Sample size calculation

The sample size was calculated based on the data results of previous research. The target sample size was 80 (20 in each group). The sample size was calculated assuming NDI means of 10.0 for patients with collars and 5.00 for patients without collars after HS and a standard deviation of 5.00 [23–25], with 5% significance (a = 0. 005) and 90% power (b = 0.90) and considering a dropout rate of 20%. The sample size was calculated using PASS 15 software.

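### The ANOVA threshold of 0.5 contradicts the plan's 0.05 level, and the open choice between unadjusted LSD and Dunnett leaves the false-positive rate anywhere from 5% to about 20%

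*Protocol article*

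**What the plan says.** The trial has four arms: no collar, and a collar for 3, 6 or 12 weeks (Study design: "wear it for 12 weeks at a ratio of 1:1:1:1"). For quantitative data, which include the primary outcome NDI, the Statistical analysis section says "We used one-way analysis of variance (ANOVA) to compare quantitative data". The next step is conditional on the ANOVA p: "< 0.5 for ANOVA, LSD or Dunnett’s test was used to compare means". The same paragraph then says that a P "value < 0.05 was considered of statistical significance", with two-sided values for comparisons of two groups.

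The Sample size calculation section also plans at 5% significance. It assumes a mean NDI of 10 with collars and 5 without, SD 5, 90% power and 20% dropout, and sets 20 patients per group. It gives one mean for all collar patients, so it assumes no difference between durations.

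**The concern.** Two things are wrong in the printed rule.

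First, a threshold of 0.5 is passed in half of all trials in which nothing differs, so it cannot act as the protective first step that LSD depends on. It also disagrees with the significance level given in the same paragraph.

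Second, the rule names LSD and Dunnett's test as alternatives and does not say which applies. LSD tests pairs without adjustment. Dunnett's test compares each group with one control and adjusts for those comparisons. They answer different questions at different error rates, and a choice left open can be made after the results are seen.

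The trial asks whether a collar helps and for how long it should be worn. A single ANOVA p does not answer the duration question; the pairwise comparisons do. The abstract says that "our findings could provide an appropriate cervical collar-wearing guideline for patients receiving HS", so a false difference between durations could reach practice advice.

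**Working it through.** **Inputs.** Four equal groups of 20, or 20 × (1 − 0.20) = 16 after the planned dropout. Pairwise level 0.05, two-sided. Planned difference (10 − 5)/5 = 1 SD. LSD uses the pooled ANOVA error, with 4 × 16 − 4 = 60 or 4 × 20 − 4 = 76 degrees of freedom. All rates are for one normally distributed outcome at one visit, by simulation (400,000 trials per setting, except where stated).

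**Step 1: what the 0.5 threshold screens out.** If the largest of the six pairwise statistics is t, the between-group sum of squares is smallest when the other two means lie midway, which gives F ≥ t²/3. LSD needs t > 2.00 at 60 df, so F > 1.33, which corresponds to an ANOVA p below about 0.27. Every trial with a significant LSD pair therefore already has p < 0.5. In the simulation the largest such p was 0.271 (16 per group) and 0.273 (20 per group). The printed threshold blocks nothing.

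**Step 2: chance of at least one false-positive pair when all four groups are equal.**

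| Procedure | Threshold 0.5 (same as none) | Threshold 0.05 |
|---|---|---|
| LSD, all six pairs | 19.9% | 5.0% |
| LSD, three pairs against no collar | 12.4% | 4.1% |
| Dunnett against no collar | 5.0% | 3.1% |
| Tukey, all six pairs | 5.0% | 4.2% |

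Results for 16 and 20 per group agree to within 0.1 percentage point. As a bound, six independent tests would give 1 − 0.95⁶ = 26.5% and three would give 1 − 0.95³ = 14.3%. The rates above are lower because the comparisons share groups.

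**Step 3: the planning scenario.** No collar is shifted by 1 SD and the three collar groups are equal. The chance that LSD declares a difference between two durations is:
- threshold 0.5: 12.1% (16 or 20 per group);
- threshold 0.05: 11.8% (16 per group) or 12.0% (20 per group).

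The corrected threshold hardly helps, because the true effect of no collar usually makes the ANOVA significant (power 81% with 16 per group and 90% with 20) and so opens the unadjusted tests between durations.

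**Step 4: price of adjustment, 16 per arm.** The standardised difference is 1/√(2/16) = 2.83. Power for one collar-versus-none pair, from the noncentral t with 60 df:
- LSD, critical value 2.00: about 79%;
- Dunnett, critical value 2.41: about 66%, with 87% to detect at least one of the three;
- Tukey over six pairs, critical value 2.64: about 58%.

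**Step 5: two families.** Dunnett at 5% for the three control comparisons plus Tukey at 5% for the three duration pairs has a combined chance of any false positive, with all groups equal, of 8.6% (16 per group) or 8.7% (20 per group), in 200,000 trials.

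**The case against.** The strongest reply is that 0.5 is a slip of the decimal point. The same paragraph uses 0.05, and the sample size section shows a similar slip, writing 5% significance as 0.005. An analyst applying the stated level would run protected LSD, which holds 5% when all groups are equal. This is probably right about the intention. But the printed rule still has to be corrected, and the 12% in the planning scenario remains after the correction.

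A reader might infer that the trial as a whole has a 20% false-positive rate in place of 5%. The documents do not support that. The 20% needs LSD to be chosen and all six pairs to be tested, and the article fixes neither. If Dunnett's test is used, the rate is 5% even with the printed threshold.

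A reader might also infer that the pairwise tests will settle which duration is recommended. The abstract says only that findings could provide a guideline, and the Study design section calls the trial exploratory. Strict control over every pair is not always required in exploratory work. That lowers the stakes, but it does not reconcile a threshold of 0.5 with a level of 0.05.

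Finally, the full protocol or an analysis plan may say when each test applies. The absence of that rule from an article would be weak ground on its own. The finding rests on what is printed: the threshold of 0.5, and LSD as an accepted procedure for four groups.

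**Conclusion.** The point stands in limited form. The threshold of 0.5 is an error in the text, probably a misprint, and contradicts the 0.05 level beside it. With the procedures it allows, the printed rule implies a false-positive rate between 5% and about 20% when no group differs, depending on which test is used and how many pairs are tested.

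Correcting the digit is necessary but does not settle the matter if LSD stays. Under the pattern that the sample size section assumes, LSD falsely separates durations in about 12% of trials with either threshold.

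These rates assume normal data, a common SD, equal group sizes, one outcome and one visit. They do not depend materially on whether 16 or 20 patients per group are analysed.

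**What to change.** In the Statistical analysis section, change 0.5 to 0.05 or drop the threshold, remove LSD, and name one adjusted procedure before the data are analysed. Dunnett and Tukey hold 5% without a preceding ANOVA test, and a 0.05 threshold in front of them only makes them more conservative (3.1% and 4.2%). Either of these would do:
- Tukey for all six pairs, as one family at 5%.
- Dunnett against no collar as the primary family, with Holm- or Tukey-adjusted comparisons between durations labelled secondary. The text should then say that the two families together carry about 8.6% error when no group differs (computed for Dunnett plus Tukey).

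The change affects wording only and needs no new patients, visits or data. The cost is power. With 16 per arm and a 1 SD difference, a single collar-versus-none comparison falls from about 79% with LSD to about 66% with Dunnett (87% for at least one of the three), or about 58% with Tukey. The chosen figure should stand next to the 90% in the Sample size calculation section, which a single pair does not reach with 16 per arm even without adjustment.

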**Methods:**

This is a randomized, single-center, prospective, parallel-controlled trial. Eligible participants will be selected according to the inclusion and exclusion criteria. The primary outcome is the neck disability index, which will be evaluated before surgery and at one week, 3 weeks, 6 weeks, 3 months, 6 months, and 12 months following surgery. The secondary outcomes consist of the Japanese Orthopedic Association Scores, MOS 36-item short-form health survey (SF-36), visual analog scale, Pittsburgh Sleep Quality Index (PSQI), Bazaz dysphagia scoring system, Falls Efficacy Scale, cervical collar satisfaction score, neck soft tissue assessment, and Braden Scale, as well as radiologic assessments for cervical lordosis, disc height of the operative levels, fusion rate, range of motion (ROM), and complications including anterior bone loss, prosthesis migration, and heterotopic ossification. The clinical and radiologic examinations were performed by investigators with no therapeutic relationship with the individual patient. All radiographs were examined by one independent radiologist.

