#### Complications

13.Anterior bone loss: It was as a combined standard of the percentage of the endplate length and implant subsidence [44] (Table 1).14.Prosthesis migration: It was defined as the sum of the change in the height of the cranial and caudal vertebral body between the immediate postoperative and follow-up situations on lateral radiographs. A level was classified as subsided if the measured subsidence was > 2 mm. Anteroposterior migration is defined as the sum of the cranial and caudal translation of the prosthesis with respect to the corresponding endplates between the immediate postoperative and follow-up situations on lateral radiographs. A prosthesis was classified as migrated if the anteroposterior migration was > 3 mm [45].15.Heterotopic ossification (HO): HO at the index level will be evaluated using the scoring system established by Mehren et al. [46] (Table 1).

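### Ordered outcomes are assigned to the Wilcoxon signed-rank test, a paired test that does not fit a comparison of four independent groups

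*Protocol article*

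**What the plan says.** The Statistical analysis section of the protocol article assigns tests by type of data. Quantitative outcomes go to one-way ANOVA with post hoc comparisons, and qualitative outcomes to chi-square or Fisher's exact test. Change within a group has its own clause: "paired sample *t*-tests were used for the same group". Ordered outcomes then get one sentence: "Comparisons of unidirectional orderly data were analyzed using the Wilcoxon signed-rank test". That sentence is not limited to change within a group, and the next one concerns two-sided p-values for differences between two groups. Neither a rank-sum (Mann-Whitney) test nor a Kruskal-Wallis test appears in the document.

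The abstract describes the design: "This is a randomized, single-center, prospective, parallel-controlled trial". Under Study design, patients are to "wear no collar, wear it for 3 weeks, wear it for 6 weeks, and wear it for 12 weeks", allocated 1:1:1:1. Sample size calculation plans 20 patients per arm and allows for 20% dropout.

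The natural candidates for ordered analysis are the dysphagia score, collected before surgery and at every visit (Table 1), and heterotopic ossification, of which the Complications section says: "HO at the index level will be evaluated using the scoring system".

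**The concern.** The signed-rank test takes the difference within each pair, ranks the absolute differences and compares the positive with the negative rank sums. It needs a reason why one observation belongs with another. Patients randomised to different collar durations have no such link. The test also takes only two samples at a time, so it cannot give an overall comparison of four arms.

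Swallowing difficulty is named as a collar harm in the Introduction and again under Data monitoring, and ossification is a listed complication. The trial hopes to inform guidance on collar wearing, so these outcomes form part of the benefit-harm comparison between arms. As written, that comparison either cannot be computed or yields a p-value that depends on row order in the data file.

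**Working it through.** No sample size, power or alpha in the document depends on this sentence, so there is no stated figure to reproduce. The check sets the design against what the test requires and then measures the consequence.

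**1. Structure.** Required: paired observations, two samples. Available: four independent arms, giving 4 × 3 / 2 = 6 pairs of arms and no pairs of patients.

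**2. Can the test be run after dropout?** Inputs: 20 per arm and 20% dropout (Sample size calculation). Assumption: dropout is independent between patients. The number remaining in an arm is then Binomial(20, 0.8), with probabilities p_k for k = 0 to 20.
- Two given arms equal: Σ p_k² = 0.158, about 16%.
- All four arms equal: Σ p_k⁴ = 0.0055, about 0.5%.

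In most cases the test cannot be computed between two arms unless patients are discarded.

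**3. If two arms are equal, does the answer depend on the pairing?** Evaluable patients: 20 × (1 − 0.20) = 16 per arm. The protocol gives no grade levels, so a four-level grade (0 to 3) is assumed. One fixed data set was used:

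| Grade | 0 | 1 | 2 | 3 |
|---|---|---|---|---|
| Arm A (n = 16) | 8 | 4 | 3 | 1 |
| Arm B (n = 16) | 4 | 4 | 5 | 3 |

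- Rank-sum test: p = 0.10, whatever the row order.
- Signed-rank test over 2,000 arbitrary pairings of the same patients: p from 0.008 to 0.247, below 0.05 in 8.5% of pairings.

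A second illustration used 20 versus 20 patients, with assumed grade probabilities 0.6/0.25/0.1/0.05 and 0.3/0.35/0.25/0.1. One simulated data set gave rank-sum p = 0.013. The signed-rank p-value ran from 0.002 to 0.057 over 2,000 pairings, with median 0.023.

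**4. How often does the verdict change?** In 300 simulated trials per scenario, with 16 per arm and 20 random pairings each, the verdict at 0.05 changed with the pairing in about 11% of trials with no difference between arms, and in about 36% under an assumed trend across arms.

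**5. Do the independent-group rank tests hold their level?** With grade probabilities 0.4/0.3/0.2/0.1 in all arms, 16 per arm and 4,000 simulations at nominal 5%, Kruskal-Wallis across four arms rejected in 4.3%, and the rank-sum test of one arm against another in 4.9%.

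**The case against.** **The sentence may mean change within a group.** It follows directly on the paired t-test clause, the signed-rank test is the usual rank counterpart of that test, and dysphagia has a preoperative value. This is possible but fits poorly. The words limiting use to the same group are attached to the t-test alone, and the paragraph otherwise allots tests by data type. Table 1 has no preoperative value for heterotopic ossification, collar satisfaction or the Braden Scale, so change from baseline cannot be formed for them. On this reading, comparisons of ordered outcomes between arms would fall to chi-square or Fisher's exact test. Those are valid but ignore the ordering. Taken alone, that would be a matter of power and of detail that could sit in an analysis plan.

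**The test is not anticonservative.** This stands. If independent patients are paired without regard to outcome, the differences are symmetric about zero when the arms do not differ. In 6,000 simulations per setting the signed-rank test rejected in 4.6% to 5.0%, against 4.6% to 5.2% for the rank-sum test. Under the alternative of the second illustration above, its power was 36% against 43% with 16 per arm, and 43% against 49% with 20 per arm. So the defect is not a raised false-positive rate. The level is protected only if the pairing is fixed without sight of the results, and nothing in the protocol fixes it.

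**The scope is narrow.** This also stands. The trial is described as exploratory, only ordered secondary outcomes are touched, no passage ties a particular outcome to this test, and the failure to run on unequal arms might expose the slip before publication.

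**Conclusion.** The concern holds: the sentence is wrong as written. It names a paired two-sample test where the design has four independent arms, and naming the wrong test differs from leaving detail to an unseen analysis plan. The mismatch follows from the design alone. The sizes rest on assumptions: the 16% and 0.5% on independent dropout at the planned rate, and the p-value ranges on an assumed four-level grade and invented category probabilities. Treating the dysphagia and ossification scores as the ordered outcomes is an inference from their description as scoring systems. The consequences are a test that usually cannot be run between arms, a result that varies with arbitrary pairing when it can, a power loss of about 6 to 7 percentage points in the illustration, and no four-arm comparison. The primary outcome, a 0 to 50 score that falls under ANOVA as quantitative data, and the sample size are unaffected.

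**What to change.** Replace the sentence with wording such as: Ordinal outcomes will be compared across the four groups with the Kruskal-Wallis test, followed by Wilcoxon rank-sum (Mann-Whitney) tests for pairs of groups with adjustment for multiplicity; the Wilcoxon signed-rank test will be used only for change within a group. A proportional-odds model with group as a factor, and baseline grade where it is collected, is a suitable alternative. It would help to list the outcomes treated as ordinal.

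The cost is one sentence of analysis wording. Data collection, sample size and the primary analysis do not change.

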### Dissemination plan

The trials results will be communicated through the presentation at academic conferences and publication in peer-reviewed medical literature.

## Discussion

External cervical brace fixation is often performed after anterior cervical surgery to provide biomechanical support to maintain spinal physiological curvature and stability, avoiding complications such as laryngeal edema and hematoma [47, 48]. There is still some debate regarding whether cervical collars should be used following surgery [24]. Previous studies have shown that the use of a cervical collar can reduce the risk of graft nonunion, graft displacement and sinking. At the same time, it can also restrict neck movement, providing spinal stability, reducing pain, and even increasing the sense of security in patients [20, 49]. Despite these benefits, some researchers have contested their validity. In their study, they found that patients with cervical pain that did not wear a cervical collar did not have a lower VAS score than those who wore a collar for 2 weeks. Moreover, the JOA score, SF-36, ROM, anterior convex angle, and complications were comparable between these two groups [50, 51]. In addition, wearing cervical collars can also bring many complications to patients, such as skin injuries skin ulcers, impaired daily activities and sleep, and decreased lung capacity and function [52–54].

Because there are no scientific clinical trials verifying the efficacy of cervical collars after hybrid surgery [20, 24, 26, 55–57], to explore the effect of wearing neck braces after undergoing hybrid surgery and discuss the best wearing time for recovery, we designed this randomized controlled trial, hoping to gain scientific and accurate results about the physical, functional, and quality of life-related outcomes of patients.

The process of osseointegration involves the direct structural and functional connection between living bone and the implant. This is normally initiated 6 weeks postoperatively, while the bone-graft bone bridge forms in around 3-month time. Therefore, most complications, including graft subsidence and loss of cervical lordosis appear during the first 6 weeks following surgery [58–60]. Thus, 3 months post-surgery is a critical time for recovery. In that case, the collar immobilization times were all set within 3 months post-surgery. Then, we adjusted the wearing time of the cervical collar to 3 weeks, 6 weeks, and 12 weeks.

Previous studies have merely selected NDI, SF-36, bone fusion rate, and imaging methods to observe the results of cervical collar wearing [20, 23–25]. In addition to selecting NDI as the primary outcome, we also designed detailed secondary indicators to monitor the possible complications caused by collar use. For instance, the JOA and the Bazaz dysphagia scoring system scoring system will be used to assess the impact of cervical collars on patients' daily life, while patients’ sleep quality will be monitored using the PSQI. Moreover, the cervical collar satisfaction score is designed to evaluate the feelings of patients with cervical collars from a subjective perspective.

Compared with previous studies [20, 23–25], we have added more details since our follow-up time may be extended to up to one year. Moreover, we used a variety of methods to evaluate the effectiveness of neck braces. Since patients often cannot return for reassessments, we opted to use phone calls for follow-ups. Radiographs and CT scans are necessary to evaluate complications and cervical imaging parameters; thus, we would allow such patients to have it done at their local hospitals. To guarantee a rigorous scientific study, patients will be screened strictly in accordance with the inclusion and exclusion criteria. Next, physicians will teach each patient how to correctly wear their neck braces to avoid unnecessary impacts on the ultimate findings. Finally, for patients who are not wearing neck braces, it is imperative that we explain the reasons in detail to reduce the placebo effect.

Nevertheless, there are several limitations to our study design. First, our trial is a single-center study; therefore, generalizing our findings to other centers should be done cautiously. Second, patients cannot be blinded in our study since the intervention is evident.

In summary, our study aims to utilize a rigorous design to comprehensively explore the effectiveness of cervical collar use by assessing various outcome measures following hybrid surgery. As a result of this trial, the feasibility of the protocol will be assessed, and a postoperative recovery strategy that is more considerate of patients and minimizes complications will be developed.

